**Fig. 1 Fig1:**
[figure not shown]
Study flow diagram

Contact data for patients selected for the intervention will be uploaded to the mPATH^®^-CRC platform via a secure file transfer protocol of a flat file to be queued for intervention delivery. It is not possible to blind patients to this type of intervention; however, the materials will be branded with their FQHC’s information, and patients will not be informed that a usual care arm exists. Similarly, usual care participants will not be informed of the study. Outcome assessors will be blinded to study arm.

### Implementation evaluation sampling, procedures

Intervention patients will be surveyed post-randomization using text messages containing links to an online survey and inviting them to rate their satisfaction with the digital outreach and services for CRC screening. All respondents will receive a $10 gift card for each survey completed.

As indicated in Fig. 2, we will conduct semi-structured interviews with providers and staff (*N* = 16 or until theme saturation is reached) and surveys with all clinic providers and staff (*n* = 210) at specified time-points. We will use purposive sampling to recruit interviewees who have the most involvement in the intervention (e.g., IT staff who assist with EHR queries, leadership who make decisions regarding clinic-level programs and practices). Administrative leaders will be asked to endorse and invite participation. Trained research staff will be interviewers for semi-structured interviews. All participants will be offered a $10 and $50 gift card for each completed survey and interview, respectively.

**Fig. 2 Fig2:**
[figure not shown]
Provider and staff data collection timeline for implementation evaluation

### Intervention and comparisons

#### Usual care arm

Patients assigned to usual care will receive the normal care and services used at the FQHC. For this clinic, this primarily involves clinical in-reach by providers during scheduled appointments to assess and recommend a screening modality including FOBT/FIT or referral for colonoscopy.

#### Intervention arm

As shown in Fig. 1, patients selected for the intervention will be sent a text message that indicates they may qualify for a CRC screening and provides a link for further information, which directs them to the mPATH^®^-CRC interface. Patients without cell phone numbers will be mailed an invitation with the same information and a tiny URL and personal code to access the interface, although we anticipate this will be < 5% of participants. Within the mPATH^®^-CRC interface, patients will first answer a series of questions to confirm CRC screening eligibility and assess for risk factors that would change screening recommendations. If eligibility for routine CRC screening is confirmed, they will view a previously validated decision aid about CRC screening that provides information about their testing options, i.e., FIT or colonoscopy. After the video, patients are given the option to “self-order” either of those tests.

The FQHC will have its own secure mPATH^®^-CRC dashboard that displays patient requests for screening tests. The mPATH^®^-CRC system automatically emails designated staff a secure link to the dashboard when new patient screening requests occur. Notices of patients who select colonoscopy will be sent to the FQHC’s referral coordinators for further scheduling and communication. To integrate with the FQHC’s FIT processing and communication, patients who select FIT will be mailed a FIT kit using the FQHC’s usual FIT and lab vendors. Any patients who fail to engage with mPATH^®^-CRC interface within approximately 2 weeks of the initial text or mailed invitation will be mailed a FIT kit by default. The research team will have access to the mPATH^®^-CRC dashboards for implementation evaluation and will assist with prompting patient follow-up care and assistance, as appropriate.

All interface materials and communication will be offered in either English or Spanish, dependent on the patient’s language preference, including the decision aid video. Participants will also have the option to view a decision aid developed and culturally adapted in partnership with tribal communities in the state [20].

### Measures

#### RCT primary outcomes

Since patients can decide between FIT or colonoscopy, the primary outcome will be CRC screening completion defined as meeting one of the following mutually exclusive pathways: (1) colonoscopy completion (regardless of indication), (2) at least one FIT test with normal FIT result, or (3) diagnostic colonoscopy following an abnormal FIT result. This measure is standard and comparable with prior CRC screening intervention studies [13, 21]. We will measure this outcome 6 months after randomization for all participants (including usual care). Outcomes will be based on encounter level data queried from the EHR, which mitigates issues of participant retention and provides pragmatic results.

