**Methods:**

Following a type 1 hybrid effectiveness-implementation design, we will conduct a patient-level randomized controlled trial (RCT) to assess the effectiveness of mPATH^®^-CRC over a three-year period. Embedded within the RCT, we will utilize a convergent, mixed methods design for evaluation of the implementation process. The planned trial sample will include 1000 patients who are at average CRC risk and due for screening. Participants will be randomized 1:1 to receive either usual care or outreach through mPATH^®^-CRC that includes text messages about screening, multi-media education on screening options, and either mailed FIT or assistance to schedule a colonoscopy. The primary outcome is completion of any CRC screening test within six months of randomization. We will also use surveys and interviews with FQHC personnel to explore integration of mPATH^®^-CRC into clinical workflows and sustainability challenges.

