### Participants

#### RCT participants

We will work with the participating FQHC to develop and validate a query of their EHR to identify patients aged 45 to 73 who are average risk for CRC, overdue for CRC screening, and have had at least one clinic visit in the past 12 months. We will exclude patients with a history of CRC or adenomas, total colectomy, family risk of CRC, or diagnosis of inflammatory bowel disease. Overdue for CRC screening is defined as no stool-based (FIT, FOBT) screening within the past one year, no stool DNA test within the past three years, and no colonoscopy within the past ten years.

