#### RCT secondary outcomes

We will also conduct a secondary analysis using years of CRC screening coverage over the three-year study period as the outcome. FIT must be repeated annually, and colonoscopy typically only needs to be repeated once every 10 years. Thus, patients will be assigned one year per annual FIT completed (e.g., FIT in years 1, 2, and 3 would be assigned 3 years; FIT in year 1 and 3 would be assigned 2 years) and up to 3 years for colonoscopy depending on the year received (e.g., colonoscopy in year 1 would be assigned 3 years, colonoscopy in year 3 would be assigned 1 year). Patients with a positive FIT result must complete a colonoscopy to count as covered. We will also collect patient-level data from the EHR record on appointment status, race, ethnicity, age, gender, insurance status, co-morbidities, and prior CRC screening to use as covariates or stratified analyses as appropriate.

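### The primary outcome and the coverage score credit only FIT and colonoscopy, although the protocol elsewhere treats FOBT and stool DNA as screening; this risks unequal under-counting between arms, of unknown direction and size

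*Protocol article*

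**What the plan says.** Five places in the protocol article bear on which tests count as screening.

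- **Abstract, Methods:** "The primary outcome is completion of any CRC screening test within six months of randomization".
- **RCT primary outcomes:** completion means one of three routes, "1) colonoscopy completion (regardless of indication), (2) at least one FIT test with normal FIT result, or (3) diagnostic colonoscopy following an abnormal FIT result". The reason given is "Since patients can decide between FIT or colonoscopy", and the measure is described as standard and comparable with earlier studies.
- **RCT participants:** being overdue requires "no stool-based (FIT, FOBT) screening within the past one year, no stool DNA test within the past three years, and no colonoscopy" within ten years. A recent FOBT or stool DNA test therefore makes a patient current.
- **Usual care arm:** providers "assess and recommend a screening modality including FOBT/FIT or referral for colonoscopy".
- **RCT secondary outcomes:** for three-year coverage, "patients will be assigned one year per annual FIT completed", and up to three years are given for colonoscopy. No other test earns credit.

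Under Intervention arm, the decision aid "provides information about their testing options, i.e., FIT or colonoscopy". Patients who do not engage within about two weeks are mailed a FIT kit by default.

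**The concern.** The operative outcome is a closed list, and FOBT and stool DNA are not on it. The stated reason for the list is the choice offered in the intervention arm, yet the list is applied to both arms. Intervention patients are steered towards tests that count. Usual-care patients receive whatever the provider recommends, and FOBT is named among the options.

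The patients affected are those whose only screen is a normal FOBT or normal stool DNA test. They are screened according to the abstract and the eligibility rule but fail the primary outcome, and that test adds nothing to their coverage score. An abnormal FOBT followed by colonoscopy is already captured by the first route.

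If such patients are more frequent in usual care, the comparison is tilted towards mPATH-CRC by the way the outcome is scored, with no difference in screening behind it. The primary test is one-sided in that same direction.

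**Working it through.** **1. The passages side by side**

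| Test | Current at eligibility | Named in usual care | Offered by mPATH-CRC | Credited in primary outcome | Credited in coverage score |
|---|---|---|---|---|---|
| Colonoscopy | yes | yes | yes | yes | yes |
| FIT | yes | yes | yes | yes | yes |
| FOBT | yes | yes | no | no | no |
| Stool DNA | yes | no | no | no | no |

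The credited list equals the intervention's menu. It differs from the eligibility list by two tests and from the usual-care list by one. The abstract's wording, taken at face value, covers all four rows.

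**2. Inputs**

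From RCT sample size and power: usual-care rate 5–12%, planned difference 5–7 points, 500 per arm, one-sided alpha 0.05, power above 80%. The share of screens done by uncredited tests is not given. Below, f is the share of usual-care screens that go uncounted and g the share of intervention screens; both are assumptions.

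**3. The plan's own figure**

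Unstratified normal approximation with pooled variance under the null:

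power = Φ{[√n·(p₂ − p₁) − 1.645·√(2p̄(1 − p̄))] / √(p₁(1 − p₁) + p₂(1 − p₂))}

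- 5% v 10%: 91.4%
- 12% v 19%: 92.2%
- 12% v 17%: 72.6%

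The stated power is reproduced at the first two pairings but not at the third. The present point does not depend on it.

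**4. Effect of uncounted screens**

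With true rates p_C (usual care) and p_T (intervention):

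observed difference = p_T(1 − g) − p_C(1 − f) = true difference + f·p_C − g·p_T

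The difference is inflated only if f·p_C exceeds g·p_T.

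*Loss in usual care only (g = 0).* The spurious addition is f·p_C:

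| f | Addition at 5% rate | Addition at 12% rate | One-sided rejection with no true effect, 5% rate | Same, 12% rate |
|---|---|---|---|---|
| 5% | 0.25 points | 0.6 points | 7.2% | 8.9% |
| 10% | 0.5 | 1.2 | 10.2% | 14.7% |
| 20% | 1.0 | 2.4 | 18.9% | 33.6% |
| 30% | 1.5 | 3.6 | 31.9% | 59.3% |

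The rejection rates come from the power formula with p₁ = p_C(1 − f) and p₂ = p_C; the nominal rate is 5%.

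*Loss in both arms:*

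- f = g = 20%, true 5% v 10%: observed 4% v 8%, so 5 points become 4.
- f = g = 20%, true 12% v 19%: observed 9.6% v 15.2%, so 7 points become 5.6.
- f = 20%, g = 10%, true 5% v 10%: observed 4% v 9%, so the difference stays at 5.
- f = 20%, g = 10%, true 12% v 17%: observed 9.6% v 15.3%, so 5 points become 5.7.

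Depending on f and g, the same omission inflates the difference, leaves it unchanged or shrinks it.

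**The case against.** A reader might infer that the trial's effect estimate is inflated. The article does not support that. Inflation needs FOBT or stool DNA to be used during the six months, and the uncounted screens to be a larger fraction of patients in usual care. No usage figure is given for either arm.

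The article also contains evidence the other way:

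- Intervention arm refers to the clinics' existing FIT processing and their usual FIT and laboratory vendors. Table 2 mentions a FIT processing laboratory and follow-up of abnormal FIT. No separate FOBT workflow is described, so the paired term in the usual-care paragraph may be a loose label for one stool test.
- Stool DNA is not named in usual care. It appears only in the eligibility look-back, which excludes people screened earlier by any route. That does not show that the clinics order it.
- Intervention patients attend the same clinics, and by design half the sample has an appointment within about 21–45 days. They can receive the same tests from the same providers.
- The abstract may be shorthand for the three routes, and the article does give a rationale for its definition.

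These points stand against any firm statement about direction or size. They do not reconcile the passages: nothing in the article says that FOBT and stool DNA are unused, or that they will be counted. Comparability with earlier studies can be kept without leaving the conflict in place.

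**Conclusion.** The point holds as an inconsistency in the definition of the primary endpoint, repeated in the coverage score, that carries a risk of differential under-ascertainment. A tilt towards mPATH-CRC is plausible because the platform and the default mailing steer patients to credited tests, but it is not established.

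Under the assumption that 5–30% of usual-care screens and no intervention screens are missed, the false difference is 0.25–1.5 points at a 5% usual-care rate and 0.6–3.6 points at 12%. The upper figure is the extreme corner of an assumed grid and should not be read as an estimate. With equal proportional loss in both arms, the true difference is understated.

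Nor should one conclude that every affected patient ends with zero years of coverage: a FIT or colonoscopy at another time in the three years would still earn credit.

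The matter goes beyond wording, because it decides which patients count as successes in the confirmatory test. It should be settled before outcomes are extracted.

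**What to change.** Use one list of accepted tests throughout:

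1. In RCT primary outcomes, count as completion, in both arms, any test that the eligibility rule accepts as screening: colonoscopy, normal FIT, normal FOBT or normal stool DNA. For scoring, treat an abnormal result on any stool test as the present definition treats an abnormal FIT.
2. In RCT secondary outcomes, apply the same list with the intervals already stated for eligibility: one year per FOBT and up to three years for stool DNA, within the study period.
3. Align the abstract with this definition.
4. Keep the FIT/colonoscopy-only definition as a sensitivity analysis.

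Alternatively, if FOBT and stool DNA are not used at this health center, state that and correct the usual-care paragraph and the abstract. The present outcome list could then stand.

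The cost is small: revised wording and additional test codes in the outcome query. The eligibility query, still to be developed and validated, must identify these tests anyway. The drawback is somewhat less direct comparability with earlier studies, which the sensitivity analysis covers. Tabulating screens by test type and arm would also show whether the omission mattered.

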### Setting

Our study will be in rural southeastern North Carolina (NC) and work directly with an FQHC in the area. The FQHC operates eight health clinics in three rural counties, all of which use Epic for their EHR. These counties are the poorest in NC in both health and economic resources [18]. The FQHC is the main safety-net provider for the low-income population and serves between 12 and 15,000 patients a year, over 6,000 of whom are eligible for CRC screening. Nearly all of the FQHC’s patients are at or below 200% of federal poverty guidelines (97%), and half are on Medicaid or Medicare, one-fourth have private insurance, and one-fourth are uninsured [19]. Patients of this FQHC are racially and ethnically diverse, including American Indian (36%), African American (30%), and Hispanic/Latino (25%) patients [19]. In 2023, 72.5% of their patients were overdue for CRC screening [19].

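### Colonoscopies done on referral may be missed by an outcome read from EHR encounters, and the loss may differ by arm in a direction the protocol does not settle

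*Protocol article*

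**What the plan says.** Under RCT primary outcomes, screening is complete with a colonoscopy for any indication, a normal FIT, or a diagnostic colonoscopy after an abnormal FIT. It is measured six months after randomization in both arms. The source is fixed there: "Outcomes will be based on encounter level data queried from the EHR, which mitigates issues of participant retention and provides pragmatic results". The Setting section identifies the record: "The FQHC operates eight health clinics in three rural counties, all of which use Epic for their EHR". No other outcome source is named.

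Colonoscopy goes by referral in both arms:
- **Usual care:** providers assess patients at scheduled visits and "recommend a screening modality including FOBT/FIT or referral for colonoscopy".
- **Intervention:** "Notices of patients who select colonoscopy will be sent to the FQHC’s referral coordinators for further scheduling and communication".

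FIT in the intervention arm runs through the FQHC's usual kit and laboratory vendors. Patients who do not engage within about two weeks are mailed a kit by default.

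The intervention arm also has a "secure mPATH^®^-CRC dashboard that displays patient requests for screening tests". The research team has access to it "for implementation evaluation and will assist with prompting patient follow-up care and assistance, as appropriate".

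On assessment, RCT sampling and procedures states: "Outcome assessors will be blinded to study arm".

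**The concern.** A FIT result returns to the FQHC through its own laboratory route. A referred colonoscopy done elsewhere enters the record only if a report comes back, and even then it need not appear as an encounter. A patient screened that way has no missing value. The patient is counted as unscreened, so no missing-data analysis would show the loss.

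This could affect the comparison by two routes:
- **Test mix.** If the arms differ in how many completions are colonoscopies, equal but incomplete capture removes different numbers from each arm.
- **Capture itself.** Notices to staff and research-team prompting exist only in the intervention arm. They could lead to fuller retrieval of its reports.

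At stake are the primary difference, planned at 5–7 percentage points with a one-sided 0.05 test, and three-year coverage. Under the coverage rule a year-1 colonoscopy is worth 3 years and one annual FIT is worth 1, so a single missed colonoscopy can cost up to three times as much as a missed FIT.

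**Working it through.** **Inputs from the protocol** (RCT sample size and power; RCT primary outcome analyses): 500 per arm; usual care 5–12%; intervention 10–35%; difference at least 5–7 points; one-sided alpha 0.05.

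**Assumptions, because the protocol gives no value:** colonoscopy share of completions *s*, and probability *c* that a completed colonoscopy is found. FIT is taken as fully captured. The protocol has no capture figure of its own to reproduce.

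**Formulas.** With true completion *p*:

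observed rate = p × [(1 − s) + s × c]

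With the same *c* in both arms (U = usual care, I = intervention):

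bias in the difference = (1 − c) × (s_U p_U − s_I p_I)

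The sign therefore depends on the absolute number of colonoscopies in each arm, not on the shares alone.

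**Check 1: equal capture, different mix.** Take s_U = 0.5, s_I = 0.2, c = 0.7. The usual-care rate is multiplied by 0.5 + 0.5 × 0.7 = 0.85 and the intervention rate by 0.8 + 0.2 × 0.7 = 0.94.

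| True rates (U vs I) | Observed rates | True difference | Observed difference | Bias (points) |
|---|---|---|---|---|
| 12% vs 17% | 10.20% vs 15.98% | 5 | 5.78 | +0.78 |
| 5% vs 10% | 4.25% vs 9.40% | 5 | 5.15 | +0.15 |
| 5% vs 12% | 4.25% vs 11.28% | 7 | 7.03 | +0.03 |
| 10% vs 25% | 8.50% vs 23.50% | 15 | 15.00 | 0 |
| 12% vs 35% | 10.20% vs 32.90% | 23 | 22.70 | −0.30 |
| 5% vs 20% | 4.25% vs 18.80% | 15 | 14.55 | −0.45 |
| 5% vs 35% | 4.25% vs 32.90% | 30 | 28.65 | −1.35 |

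The first and last rows are the extremes for rates in the stated ranges with a gap of at least 5 points. In relative terms, +0.78 is 15.6% of a 5-point effect and −1.35 is 4.5% of a 30-point effect.

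**Check 2: no true effect, same shares.** Both arms truly 10%, c = 0.7: observed 8.5% and 9.4%, a spurious 0.9 points.
- Pooled rate 8.95%; null SE = √(2 × 0.0895 × 0.9105 / 500) = 0.01805. The unpooled SE is the same to four figures.
- z = (1.645 × 0.01805 − 0.009) / 0.01805 = 1.146, so the one-sided rejection probability is 12.6%.
- At c = 0.9 (9.5% vs 9.8%) it is 6.9%. At c = 0.5 (7.5% vs 9.0%) it is 21.7%.

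This case implies 5% of usual-care patients but only 2% of intervention patients having a colonoscopy.

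**Check 3: same mix, different capture, no true effect.** Spurious difference = p × s × (c_I − c_U), for p from 5% to 12% and s from 0.3 to 0.7.
- Capture 80% in both arms: 0 points, type I error 5.0%.
- 90% (U) vs 100% (I): 0.05 × 0.3 × 0.10 = 0.15 points up to 0.12 × 0.7 × 0.10 = 0.84 points; type I error 6.2% to 10.9%.
- 80% (U) vs 95% (I): 0.05 × 0.3 × 0.15 = 0.225 points up to 0.12 × 0.7 × 0.15 = 1.26 points; type I error 7.0% to 15.7%.

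If capture were better in usual care, the sign would reverse.

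**The case against.** The strongest reply is that the document shows no differential capture. Intervention requests go to the FQHC's own referral coordinators, and nothing says usual-care referrals bypass them or go untracked. The dashboard shows requests, not completions, and is not named as an outcome source. The outcome rule and time point are the same in both arms, and assessors are blinded. Prompting that produces more completed tests is part of the intervention effect, not ascertainment bias.

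All of that stands. It defeats the stronger reading a reader might infer: that usual-care colonoscopies are more easily missed and the effect is therefore inflated. Check 1 shows zero or negative bias over much of the anticipated range. The null case in Check 2 needs outreach that offers self-ordered colonoscopy to yield 60% fewer colonoscopies than usual care (2% against 5%).

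It does not remove the weaker point. Blinding and a common rule prevent biased judgment, but they cannot recover a report that never reached the record.

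A second reply is that the plan already relies on this EHR for colonoscopy history: eligibility looks back ten years through a query to be validated. That suggests some outside colonoscopies are on file. It does not show that they appear as encounters, which is the source named for the outcome.

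A third reply is that retrieval detail belongs in the full protocol. That would hold if the article were silent, but it names a specific and narrow source. Its remark on retention is fair as far as loss to study contact goes and need not be deleted. It simply does not address screening done elsewhere.

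**Conclusion.** The point holds as a risk of outcome misclassification that may differ by arm, not as a demonstrated inflation of the effect. The encounter-only source, read with referral for colonoscopy in both arms, allows a completed colonoscopy to be scored as not screened.

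Under the assumed shares of 50% and 20% and 70% capture in both arms, the bias runs from about +0.8 to −1.4 points. The upward cases fall where the true difference is small and matter most to the conclusion. Type I error is about 12.6% if true completion is 10% in both arms. If capture also favoured the intervention arm, moderate gaps would add roughly 0.2 to 1.3 points.

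All of these figures rest on assumed shares and capture rates. The article does not say who performs colonoscopies or how reports return. The three-year coverage outcome is exposed to the same fault, with more weight on each missed colonoscopy.

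This is a worthwhile, inexpensive improvement, useful whichever way the bias runs.

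**What to change.** In RCT primary outcomes:
1. Define colonoscopy completion from any dated evidence in the FQHC's Epic record: encounters, outside reports, scanned results and closed referrals.
2. At six months, have the blinded outcome assessors check every colonoscopy referral still open in either arm, by one identical procedure, from a list without arm labels.
3. State that screening recorded only outside this record counts as not completed.

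The cost is a broader query and some abstraction time, limited to patients with an open referral and done by assessors already planned. Sample size, eligibility and the main test do not change.
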